#### Analysis of secondary outcomes

Secondary outcomes will be analysed by standard parametric or non-parametric procedures as appropriate. Ninety five per cent confidence intervals will be presented for treatment effects.

The proportion of participants who discontinue with the interventions will be summarised by reason and by intervention group. Results will be reported according to the CONSORT Statement (CONSORT statement 2010) [20].

#### Analysis of ultrasound data

For the sub-group of 20 participants, ninety five per cent confidence intervals will be calculated and presented for resting and automatic activation thickness of transversus abdominus and internal oblique muscles. The effect of type of intervention over time will be tested using analysis of variance at the two-tailed 5% level. We will also undertake a preliminary exploration as to whether factors such as type and duration of diagnosis may impact on physiological state of the core muscles.

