**Methods:**

This is a multi-centre, double blind, block randomised, controlled trial. Eligible participants will be recruited from 4 UK centres. Participants will be randomly allocated to one of three groups: Pilates based core stability training, standardised physiotherapy exercise or contract-relax relaxation sessions (placebo control). All will receive face to face training sessions over a 12 week period; together with a 15 minute daily home programme. All will be assessed by a blinded assessor before training, at the end of the 12 week programme and at 4 week follow-up. The primary outcome measure is the 10 metre timed walk. Secondary outcome measures are the MS walking Scale (MSWS-12), the Functional Reach (forwards and lateral), a 10 point Numerical Rating Scale to determine "Difficulty in carrying a drink when walking", and the Activities-specific Balance Confidence (ABC) Scale. In addition, ultrasound imaging of the abdominal muscles will be performed before and after intervention to assess changes in abdominal musculature at one of the four centres (Plymouth).

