### Participant recruitment and group allocation

The Lanarkshire, Newton Abbot and London centres will each recruit 20 participants, and the Plymouth centre will recruit 40 participants.

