#### Participants will be recruited via either

i the physiotherapy department at each of the participating NHS centres, or

ii the SWIMS (South West Impact of MS) database in the case of participants living in the Devon region. SWIMS is a population - based database in which longitudinal data is being collected to assess the impact of MS on over 1100 people in Devon and Cornwall, UK. It is run by the Clinical Neurology Research Group, Peninsula Medical School, Universities of Exeter and Plymouth. Potential participants recruited via this avenue will be made aware of this study in two ways; either by an advertisement placed in the twice yearly newsletter which is sent by the SWIMS team to people with MS who are registered on the database; or via a letter of invitation by the Chief Investigator of SWIMS to participants meeting the inclusion criteria. In either case, the study team contact details will be provided to enable interested SWIMS participants to find out more about the study or in taking part. Under the Data Protection Act, the SWIMS team will not pass on any information about SWIMS participants to the core stability study team. It is only once the core stability team have been contacted by the potential participant that they will begin the recruitment and consent process.

Interested participants will be provided with an information pack describing the study; this will be supported by verbal information when requested. Participants will be screened for eligibility by the principal investigators at each site, who will gain written informed consent for those who meet the inclusion criteria.

After consenting to participate and before intervention, participants will be randomised by the principal investigators at each site to one of three groups -intervention A (Pilates based core stability training), intervention B (standardised physiotherapy exercises) or control intervention C (relaxation). A block randomisation procedure (whereby each site is the block) will be used with central concealment through the use of numbered tickets placed in sealed opaque envelopes, organised by the study co-ordinator. The investigators will open the sealed envelopes sequentially and only after the participant's name and other details are written on the appropriate envelope.

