#### Measures to explore the underlying mechanisms of change

In addition to the clinically based functional outcome measures, in a sub-group of 20 subjects based at Plymouth University, automatic activation of the deep abdominal core stabilising muscles using ultrasound imaging will be measured before (0 weeks) and immediately after completion of the intervention programme (12 weeks). Measurement of abdominal muscle thickness changes during exercise have been shown to be valid measures of muscle activity [17,18]. Measuring both the resting thickness and thickness upon muscle activation in the transversus abdominus and internal oblique muscles will allow us to determine whether differences in the outcomes of the three interventions exist at an impairment level. This will provide important information pertaining to the mechanisms underlying any functional changes which may be observed to occur.

Current literature suggests that 20 hours training are needed to ensure the acquisition and measurement of ultrasound images is reliable for this purpose [19]. Following 20 hours of training, an intra-rater reliability study will be undertaken to establish reliability of ultrasound measurements on repeated testing. A standardised protocol will be used for image acquisition. Images for each of the first 20 consecutive participants at Plymouth University will be taken before and after the intervention period. Participants will be imaged in supine, both at rest and with an active straight leg raise of their strongest leg to automatically activate the deep abdominal muscles [17]. The ultrasound transducer will be placed on the mid axillary line in between the 12^th ^rib and iliac crest on the contralateral side to the leg being lifted. Participants will lie in supine with arms crossed resting on their chest. An image clip will be taken during quiet respiration (image at rest) and then a command will be given to lift the contralateral leg 5 cm at which time a further image clip will be recorded (image of automatic muscle activation). This procedure will be repeated 3 times. The ultrasound image clips will be transferred to a computer and analysed off-line, where the thickness of the transversus abdominus and internal oblique muscles will be measured as a measure of muscle size and activity during both quiet respiration and automatic activation [17].

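### The ultrasound sub-study is said to determine whether three interventions differ, but about seven people per arm give 80% power only for differences near 1.6 SD; it should be worded as exploratory estimation

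*Protocol article*

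**What the plan says.** In the protocol article, the section on measures to explore mechanisms of change places the imaging "in a sub-group of 20 subjects based at Plymouth University". The people are taken in order of entry: "Images for each of the first 20 consecutive participants at Plymouth University will be taken before and after the intervention period". Resting and activated thickness of two muscles, transversus abdominus and internal oblique, are measured at 0 and 12 weeks. The section says that these measurements "will allow us to determine whether differences in the outcomes of the three interventions exist at an impairment level".

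The section on analysis of ultrasound data plans 95% confidence intervals for the thicknesses and then a test: "The effect of type of intervention over time will be tested using analysis of variance at the two-tailed 5% level". In that section, only the look at type and duration of diagnosis is called preliminary and exploratory; the arm comparison carries no such label. The abstract, by contrast, lists the third aim as exploring mechanisms. The Background makes the ultrasound question a further secondary aim and again speaks of determining whether change occurs.

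The only power statement in the article concerns the 10 metre timed walk: 30 per group, power 0.85, α = 0.05.

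**The concern.** The verb promises an answer in both directions: either the interventions differ at impairment level or they do not. A 5% test on 20 people in three arms can give a positive answer only if the difference is very large. It cannot give a negative answer unless the interval around the difference is narrow, and here it will be wide.

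At stake is the interpretation of a named secondary aim. If the test is non-significant, a report that keeps to the protocol's wording could state that no impairment-level difference exists. The data would be compatible with differences of more than one SD either way. The primary outcome and its analysis are not affected.

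**Working it through.** **Inputs from the protocol article**
- 20 people imaged, all at Plymouth (measures to explore mechanisms).
- Three arms: "Participants will be randomly allocated to one of three groups" (abstract). Equal allocation is assumed, so 20/3 = 6.7 per arm, or 7/7/6.
- Two-tailed α = 0.05 (analysis of ultrasound data).
- Drop-out of 10% (sample size section).
- The SD of thickness change and a target difference are not given. The difference is therefore expressed as d, in SDs of the change score, and shown over a range.

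**The plan's own figure.** There is no sample size calculation for the ultrasound. The main-trial figure of 30 per group cannot be reproduced, because no SD is stated. Solving backwards, 30 per group with 85% power and two-sided 5% corresponds to d of about 0.79 (t-based). The drop-out step does reproduce: 90/0.9 = 100.

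**Power of the stated test.** With two time points, the arm-by-time ANOVA is a one-way ANOVA on change scores. Power comes from the noncentral F distribution with 2 and 17 degrees of freedom, with one arm differing from the other two by d. At 7/7/6:
- d = 0.5: 13%
- d = 0.79 (the main trial's implied effect): 26%
- d = 0.8: 27%
- d = 1.0: 40%
- d = 1.5: 75%
- d = 2.0: 95%

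The ANOVA reaches 80% power at d = 1.59 if one arm stands apart, and at d = 1.89 if the three arms are evenly spread. With 10% drop-out (18 people, 6/6/6) these become 1.72 and 1.99, and power at d = 0.8 falls to about 24%.

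**Pairwise comparison, 7 v 7.** The noncentrality is d/√(1/7 + 1/7).
- Two-arm error (12 df): 80% power at d = 1.63; power 0.28 at d = 0.8.
- Error pooled over three arms (17 df): 80% power at d = 1.59; power 0.29 at d = 0.8.

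**Width of the interval.** The half-width of the 95% confidence interval for a pairwise difference is t(0.975, 17) × √(2/7) = 2.110 × 0.535 = 1.13 SD. An observed difference of zero would still be compatible with a true difference of up to 1.13 SD in either direction.

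**Arm split.** The article describes "A block randomisation procedure (whereby each site is the block" and says that "the Plymouth centre will recruit 40 participants". If Plymouth is a single block of 40 with no smaller blocks inside it, and its allocation is 14/13/13 (both assumed), the first 20 split exactly 7/7/6 with probability 0.21, and the smallest arm has four or fewer with probability 0.22. With 4 v 8, the pairwise difference for 80% power is 1.90 (two-arm error) or 1.82 (pooled error). The even split used above is thus the favourable case.

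**Gain from adjusting for baseline.** Let r be the correlation between baseline and 12-week thickness. The ratio of ANCOVA variance to change-score variance is (1 − r²)/(2(1 − r)) = (1 + r)/2. It is multiplied by about 1 + 1/15 = 1.067 for estimating the slope in 20 people. The values of r are assumed.
- r = 0.5: 0.75 × 1.067 = 0.80, about 20% lower
- r = 0.8: 0.90 × 1.067 = 0.96, about 4% lower
- r = 0.9: 0.95 × 1.067 = 1.01, about 1% higher

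The detectable difference of 1.59 would become about 1.59 × √0.80 = 1.42 at r = 0.5, and 1.59 × √0.96 = 1.56 at r = 0.8. ANCOVA helps a little but does not make the sub-study decisive, so the claim has to change as well.

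**The case against.** The strongest reply is that the exploratory status is already visible. The abstract speaks of exploring, the measures section has exploration in its heading, the ultrasound analysis mentions confidence intervals before the test, and the primary outcome is the walk. No sentence plans to read a non-significant result as no difference. Arm-by-time ANOVA is also valid under randomisation and matches the change-score comparison chosen for the primary analysis, so ANCOVA is a matter of efficiency, and the gain is small. This stands, and it is why the point is minor. It does not remove the inconsistency between an aim of exploring and a statement that the measurements will settle the question.

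Several stronger readings are tempting, and the document does not support them:
- *The sub-study cannot detect any difference.* It can, if the difference is about 1.6 to 2 SD, and the SD is not known.
- *Four unadjusted tests give a 19% chance of a false positive.* Two muscles in two states suggest four measures, but no count of tests is stated, and one model with muscle and state as factors would also fit the text. The ultrasound section is silent on multiplicity; the statement against adjustment concerns the primary outcomes. The figure 1 − 0.95⁴ = 18.5% assumes independence; simulation gives about 16% at correlation 0.5 and about 10% at 0.9.
- *No key measure is named and no analysis links muscle change to walking.* A condensed article may leave both to the full protocol or analysis plan. A regression on 20 people would itself have 80% power only for a correlation of about 0.59 or more.
- *The two scans may be of opposite sides.* The scan is done "with an active straight leg raise of their strongest leg", with the opposite side imaged. The text does not say that the stronger leg is chosen again at 12 weeks, and the standardised image-acquisition protocol is not shown.
- *The early Plymouth envelopes should be re-ordered to balance the 20.* That alters main-trial allocation for the sake of a sub-study and could make later allocations easier to guess at a site where investigators open the envelopes. Perfect balance would still leave the detectable difference near 1.6 SD.

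**Conclusion.** The point holds in a limited form. The wording of the ultrasound claim outruns what 20 people in three arms can show. The stated ANOVA has 80% power only for differences of about 1.6 SD of change, and about 28% at 0.8 SD. The 95% interval for a pairwise difference extends about 1.1 SD either side, so a null result cannot support equality at impairment level.

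These figures assume roughly equal arms, complete scans and normally distributed changes. Drop-out or an uneven split makes them worse. Because the SD of thickness change is not given, they say nothing about how likely a difference of that size is. Severity: minor. It concerns one secondary aim and can be settled by wording and a small change of model.

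**What to change.** 1. In the analysis of ultrasound data, replace the arm-by-time ANOVA with ANCOVA: 12-week thickness as outcome, arm as factor, baseline thickness as covariate. Present the between-arm estimates with 95% confidence intervals first.
2. In the section on measures to explore mechanisms, change *determine* to *estimate*, label the arm comparison exploratory as the abstract does, and state that a non-significant result does not exclude a difference.

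Optional: state that the leg lifted and the side imaged at 12 weeks are those used at baseline. This clarifies the procedure and does not correct a demonstrated error.

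The cost is one error degree of freedom (17 to 16), a few sentences and a more modest claim. No further participants or scans are needed, and randomisation is left as it is. If the pre-post correlation is as high as 0.9, ANCOVA brings no gain in precision and a loss of about 1%.

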## Discussion

Currently there is scant evidence regarding the effectiveness of Pilates based core stability exercise on the balance and mobility of people with MS. It has been suggested that people need to have a level of "body awareness skills" to be able to effectively achieve this voluntary activation of the core stabilisers [6]. This may be particularly difficult for people with MS who can experience a range of sensory, proprioceptive and motor impairments. It is possible that these issues and others (for example the limited face to face contact time that physiotherapists may have with clients) may limit the application of this exercise approach within routine clinical practice. It is also possible that the benefits gained are no greater than that achieved by relatively simple strengthening programmes that load the lower limb, which are frequently provided by therapists of all skill levels within routine clinical practice.

This trial is pragmatic in nature, hence the intention is that the conclusions drawn from the data generated will be directly transferable to clinical practice. Policy makers and therapists implementing physiotherapy programmes will benefit from the results of the trial, by an enhanced evidence base in this area. So too will people with MS who spend time and energy undertaking these exercise regimes, and may choose to self-finance participation in Pilates training programmes. Participants in the trial will only be included if ambulatory (4.0 - 6.5 EDSS) hence it may not be possible to extrapolate the results to less mobile people with MS.

## Conclusions

The results of this clinical trial will show the effect of a 12 week Pilates based core stability programme and a standard physiotherapy exercise programme, in comparison to a placebo control group on subjective and objective measures of balance and mobility in ambulatory people with MS. In addition, the underlying mechanisms of change in the deep abdominal musculature will be evaluated in a sub-set of individuals, with ultrasound imaging.
